## Secondary endpoints

### Cohort 1

***Efficacy***

- The time to the first clinical episode of symptomatic *P falciparum* malaria (Secondary Case Definition 1 as defined in section 10.1) detected by passive case detection over a 6 month observation period starting 14 days after dose 3 (day 90) in children (1-4 years of age at first vaccination) who have received RTS,S/AS02A malaria vaccine or one of the control vaccine schedules (either hepatitis B vaccine or *Haemophilus influenzae* type b vaccine and 7-valent pneumococcal conjugate vaccine).
- The time to the first clinical episode of symptomatic *P falciparum* malaria (Secondary Case Definition 2 as defined in section 10.1) detected by passive case detection over a 6 month observation period starting 14 days after last vaccination (dose 3) in children (1-4 years of age at first vaccination) who have received RTS,S/AS02A malaria vaccine or one of the control vaccine schedules (either hepatitis B vaccine or *Haemophilus influenzae* type b vaccine and 7-valent pneumococcal conjugate vaccine).
- The time to the first clinical episode of symptomatic *P falciparum* malaria (Secondary Case Definition 3 as defined in section 10.1) detected by passive case detection over a 6 month observation period starting 14 days after last vaccination (dose 3) in children (1-4 years of age at first vaccination) who have received RTS,S/AS02A malaria vaccine or one of the control vaccine schedules (either hepatitis B vaccine or *Haemophilus influenzae* type b vaccine and 7-valent pneumococcal conjugate vaccine).
- The total number of clinical episodes of symptomatic *P falciparum* malaria (according to the Primary Case Definition for malaria episodes as defined in section 10.1) over the time at risk (as defined in section 10.7.2.1) during the 6 -month surveillance period (month 2½ to month 8½ inclusive).
- The time to the first presentation at Manhiça District Hospital with anaemia (Anaemia Case Definition as defined in section 10.1) over a 6 month observation period starting 14 days after last vaccination (dose 3) in children (1-4 years of age at first vaccination).
- Presence of anaemia in children (1-4 years of age at first vaccination) (Anaemia Case Definition as defined in section 10.1) at 6½ months after dose 3 (month 8½).
- The number of asexual stage falciparum parasites per µl of blood for each subject at 6½months after dose 3 (month 8½).

***Safety***

- Occurrence of solicited symptoms after each vaccination over a 4-day follow-up period (day of vaccination and 3 subsequent days).
- Occurrence of unsolicited symptoms after each vaccination over a 30-day follow-up period (day of vaccination and 29 subsequent days).
- Occurrence of serious adverse events from the time of first vaccination (month 0) until 6½months post dose 3 (month 8½).

***Immunogenicity***

- Titres of anti-CS antibodies at the following time points for which serology samples are analyzed: day 0, day 90 and month 8½.

### Cohort 2

***Efficacy***

- The time to first malaria infection (first recording of infection of asexual stage falciparum parasites detected by the active detection of infection surveillance or passive case detection, see section 5.2.6) over a period starting 14 days after last vaccination and until 6½months after last vaccination (month 8½).

***Safety***

- Occurrence of solicited symptoms after each vaccination over a 4-day follow-up period (day of vaccination and 3 subsequent days).
- Occurrence of unsolicited symptoms after each vaccination over a 30-day follow-up period (day of vaccination and 29 subsequent days).
- Occurrence of serious adverse events from the time of first vaccination (month 0) until 6½ months post dose 3 (month 8½).

***Immunogenicity***

- Titres of anti-CS antibodies at the following time points for which serology samples are analyzed: days 0, 60 and 90, month 8½.
- Titres of anti-HBs antibodies at the following time points for which serology samples are analyzed: days 0 and 90, month 8½.

## Tertiary Endpoints

### Cohort 1

***Efficacy***

- The total number of clinical episodes of symptomatic *P falciparum* malaria (according to the Primary Case Definition for malaria as defined in section 10.1) over the time at risk (as defined in section 10.7.2.1) during the open surveillance period (months 8½ to 21).
- The total number of clinical episodes of symptomatic *P falciparum* malaria (according to the Primary Case Definition for malaria as defined in section 10.1) over the time at risk (as defined in section 10.7.2.1) during the complete surveillance period (months 2½ to 21).
- Presence or absence of anaemia in children aged 1-4 years of age at first vaccination (Anaemia Case Definition as defined in section 10.1) at month 21 (day 630).
- The number of asexual stage falciparum parasites per µl of blood for each subject at 19 months after dose 3 (month 21).

***Safety***

- Occurrence of serious adverse events during the single-blind surveillance period (from month 10 to month 21 inclusive).

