|  | Efficacy:   - The total number of clinical episodes of symptomatic *P falciparum* malaria (according to the Primary Case Definition for malaria as defined above) over the time at risk during the single-blind surveillance period (months 8½to 21). - The total number of clinical episodes of symptomatic *P falciparum* malaria (according to the Primary Case Definition for malaria as defined above) over the time at risk during the complete surveillance period (months 2½ to 21 inclusive). - Presence of anaemia in children (1-4 years of age at first vaccination) (Anaemia Case Definition as defined above) at 19 months after dose 3 (month 21). - The number of asexual stage falciparum parasites per µl of blood for each subject at 19 months after dose 3 (month 21).   Safety:   - Occurrence of serious adverse events during the single-blind surveillance period (from month 8½ to month 21).   Immunogenicity:   - Titres of anti-CS antibodies at the following time point for which serology samples are analysed: month 21. | |
| **Tertiary endpoints: Cohort 2** | | |
|  | Safety:   - Occurrence of serious adverse events during the single-blind surveillance period (from month 8½ to month 21).   Immunogenicity:   - Titres of anti-HBs and anti-CS antibodies at the following time point for which serology samples are analyzed: month 21. | |

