***Safety***

- To assess in children (1 to 4 years of age at first vaccination) the safety of the RTS,S/AS02A malaria candidate vaccine during months 8½ to 21.

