***Immunogenicity***

- To assess the humoral immune response to the CS antigen of the RTS,S/AS02A malaria candidate vaccine at 19 months post dose 3 (month 21) in children (1 to 4 years of age at first vaccination).

See Section 10.4.1 for delineation of tertiary endpoints for Cohort 1.

### Cohort 2

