  **(Amended January 17, 2003)**
- Enrolment will be performed within 12 weeks.
- Controlled:
- 3 doses of hepatitis B vaccine (Engerix‑B™) to children of ***24*** ~~18~~ months and older.
- 2 doses of a 7-valent pneumococcal conjugate vaccine (Prevnar®, Wyeth Lederle Vaccines) at first and third vaccination and 1 dose of Haemophilus influenzae type b vaccine (Hiberix™) at second vaccination to children less than ***24*** ~~18~~ months. **(Amended January 17, 2003)**
- 3 doses of vaccine (RTS,S/AS02A or control) will be administered using a 0, 1 and 2 month vaccination schedule.
  A full dose (0.5 ml) of the control vaccine or a paediatric dose (0.25 ml dose volume) of the RTS,S/AS02A vaccine will be administered at each vaccination.
- Blinding:
- Vaccination and surveillance period (double-blind phase) from month 0 to the data lock point for primary and secondary objectives (month 8½).
- Single-blind surveillance period (study subjects will remain blinded to treatment allocation until study end as will study staff responsible for endpoint evaluation at health facilities and at cross-sectional surveys) from month 8½ to data lock point for analysis of tertiary objectives (month 21).
- Subjects will be randomly assigned in a 1:1 fashion to receive either the RTS,S/AS02A candidate malaria vaccine or one of the control vaccine regimes. See Section 6.4 for a detailed description of the randomization method.
- Two cohorts will evaluate the effect of the malaria candidate vaccine on clinical malaria disease and malaria infection (Cohorts 1 and 2 respectively, with 1564 subjects in Cohort 1 and ***416*** ~~356~~ subjects in Cohort 2). In Cohort 2 where the efficacy of the vaccine against infection will be evaluated, subjects will receive 4 weeks prior to onset of surveillance one dose of sulfadoxine-pyrimethamine and amodiaquine per day for 3 days, so as to clear any parasitaemia. **(Amended January 17, 2003)**
- Self-contained study, i.e. this study will be independent of other studies.
- Data collection will be by electronic remote data entry (RDE)

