# Data Evaluation: criteria for evaluation of objectives

A reporting and analysis plan (RAP) will be developed by CISM and GSK Biologicals in consultation with MVI and submitted to the DSMB for approval prior to breaking the study blind.

For the purposes of data analysis, there will be two distinct data lockpoints for the study, irrespective of cohort:

- Month 8½ (day 256): at the end of the surveillance period for the primary and secondary objectives, double-blind phase.
- Month 21 (day 630): at the end of the safety and efficacy follow-up, open phase. This data lockpoint will be used for the analysis of tertiary objectives.

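### Section 10.4.1 starts the Cohort 1 tertiary SAE window at month 10 instead of month 8½, so the section 10 endpoint definitions do not meet

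*Supplement*

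**What the plan says.** The Cohort 1 SAE endpoints in section 10 come in two parts.

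- **Secondary (section 10.3.1, Safety):** "Occurrence of serious adverse events from the time of first vaccination (month 0) until 6½months post dose 3 (month 8½".
- **Tertiary (section 10.4.1, Safety):** "Occurrence of serious adverse events during the single-blind surveillance period (from month 10 to month 21 inclusive".

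Other parts of the protocol give the second window differently.

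- **Synopsis, tertiary endpoints for Cohort 1:** "Occurrence of serious adverse events during the single-blind surveillance period (from month 8½ to month 21". Section 10.4.2 gives the same window for Cohort 2.
- **Section 2.3.1, tertiary safety objective for Cohort 1:** "the safety of the RTS,S/AS02A malaria candidate vaccine during months 8½ to 21". The end of that section sends the reader on: "See Section 10.4.1 for delineation of tertiary endpoints for Cohort 1".
- **Section 3, definition of the single-blind phase:** "from month 8½ to data lock point for analysis of tertiary objectives (month 21".
- **Section 10, opening, first data lock point:** "Month 8½ (day 256): at the end of the surveillance period for the primary and secondary objectives, double-blind phase". The second lock point is month 21, day 630.

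The first efficacy endpoint in section 10.4.1, just above the safety endpoint, also starts its second-period window at month 8½.

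**The concern.** The two Cohort 1 SAE endpoints should together cover the time from first vaccination to month 21. As section 10 is worded, they do not: one closes at month 8½ and the next opens at month 10. Section 10.4.1 also contradicts itself, because it attaches a month 10 start to a period that the protocol begins at month 8½. No visit, lock point or rationale is tied to month 10.

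The synopsis has the month 8½ start, but section 2.3.1 names section 10.4.1 as the place where these endpoints are set out. The month 10 figure therefore sits in the operative definition. Occurrence of SAEs, deaths included, is a named endpoint, and Cohort 1 is 1564 of 1980 children (79%). If the definition is followed literally, an event in the interval has no endpoint to belong to, and the Cohort 1 window differs from the Cohort 2 window. The window is better settled before data are seen than after.

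**Working it through.** **Start of the second SAE window, by source**

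| Source | Start |
| --- | --- |
| Section 10.4.1, Cohort 1 endpoint | month 10 |
| Synopsis, same Cohort 1 endpoint | month 8½ |
| Section 2.3.1, Cohort 1 objective | month 8½ |
| Section 3, single-blind phase | month 8½ |
| Section 10.4.2, Cohort 2 endpoint | month 8½ |

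The first window ends at month 8½ in section 10.3.1. Only section 10.4.1 is out of line.

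**Calendar.** The opening of section 10 equates month 21 with day 630, so one month is 630/21 = 30 days. Month 8½ is then 8.5 × 30 = 255 days, against the stated day 256. The schedule in section 5.3 agrees, with months 1, 2 and 3 at days 30, 60 and 90. The protocol thus uses month numbers as time points.

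**Length of the interval**

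- Month 10 as a time point: 10 × 30 = day 300, and 300 − 256 = 44 days, or 44/7 = 6.3 weeks.
- Month 10 as the tenth month, starting at the end of month 9: 9 × 30 = day 270, and 270 − 256 = 14 days, or 2 weeks.
- As a check with 30.44-day calendar months: 304.4 − 256 = 48 days. The protocol does not count this way.

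**Share of the second period.** The period runs 630 − 256 = 374 days, and 44/374 = 12%.

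**Child-years, upper bound.** All 1564 Cohort 1 children are taken as still followed.

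- 44 days: 1564 × 44/365 = 189.
- 14 days: 1564 × 14/365 = 60.

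Section 10.6.1 allows for 10% non-evaluable subjects, so the true follow-up may be lower.

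**After correction.** With a month 8½ start, the windows meet at day 256 and the interval is 0 days.

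**The case against.** The strongest reply is that this is a wrong figure in a parenthesis with an obvious resolution. Section 10.4.1 names the right period, the synopsis covers every event in the interval, and the endpoint is tertiary and descriptive, with no test, sample size or decision rule attached. That stands, and it limits the severity. It does not remove the contradiction in the section designated to define the endpoint.

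Three stronger readings are tempting, and the documents support none of them.

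- **That SAEs would be lost, or would necessarily drop out of the analysis.** Section 8.1 requires SAE recording from first dose to 19 months after the last dose. Section 5.2.8 provides monthly home visits, and section 5.1.3.2 sends all SAEs to the DSMB as received. Section 10.7.3 describes SAEs in the Total Cohort with no time window. The reporting and analysis plan, which would fix the tables, is not among the documents.
- **That pooled counts across cohorts would mix windows.** The protocol specifies no pooled SAE count with a window, so this is conjecture.
- **That the interval falls just after unblinding.** Section 6.5.1 breaks the blind only after the double-blind phase is complete and the database is locked, and section 3 allows 12 weeks (84 days) for enrolment. If enrolment takes the full span, the last child reaches day 256 on study day 84 + 256 = 340. A child enrolled before study day 340 − 300 = 40 has by then already passed day 300. For roughly the first half enrolled, the interval precedes unblinding.

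**Conclusion.** The point holds as an internal contradiction in a safety endpoint definition. Section 10.4.1 starts the Cohort 1 tertiary SAE window at month 10, against its own named period, the synopsis, section 2.3.1, section 3 and the Cohort 2 endpoint. Taken with section 10.3.1, the section 10 definitions leave about 44 days in neither Cohort 1 SAE endpoint, at most about 189 child-years. That figure rests on the protocol's 30-day month, on reading month 10 as a time point, and on full follow-up of 1564 children. On the tenth-month reading it is 14 days and at most about 60 child-years.

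What is undefined is the endpoint to which these events belong and the table in which they appear. Their collection and description are not in doubt, and the primary and secondary results are untouched. Severity is minor. The month 10 figure is most likely text left unrevised, though the documents do not say so.

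**What to change.** In section 10.4.1, Safety, change the start of the window from month 10 to month 8½, so that it runs to month 21 as in the synopsis, section 2.3.1, section 3 and section 10.4.2. The reporting and analysis plan should carry the same window. The cost is one figure in the protocol, with no new visits, data or sample-size work, because recording already covers the interval.

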***Immunogenicity***

- Titres of anti-CS antibodies at the following time point for which serology samples are analysed: month 21.

### Cohort 2

***Safety***

- Occurrence of serious adverse events during the single-blind surveillance period (from month 8½ to month 21).

***Immunogenicity***

- Titres of anti-HBs and anti-CS antibodies at the following time points for which serology samples are analyzed: month 21.

## Study groups/data sets to be evaluated

Analyses will be performed on subjects in the Total and According to Protocol (ATP) Cohorts.

***Total cohort for analysis of efficacy***

The Total Cohort will include all subjects enrolled in the study who received at least one dose of the candidate malaria vaccine or control vaccine and for whom data concerning efficacy endpoint measures are available. Note that for the primary endpoint of the trial only those children in Cohort 1 will contribute.

***Intention-to-treat cohort for analysis of vaccine efficacy***

As for the Total Cohort for analysis of vaccine efficacy, the intention-to-treat cohort for analysis of vaccine efficacy will include all subjects enrolled in the study who received at least one dose of the candidate malaria vaccine or control vaccine and for whom data concerning efficacy endpoint measures are available. However, in contrast to the Total Cohort, this cohort will be used specifically for analysis of vaccine efficacy over the period of time at risk starting from first vaccination (day 0) (see Section 10.7.2.2.9).

***Protocol-defined cohort for analysis of efficacy (ATP)***

The protocol-defined cohort for analysis of efficacy will include all evaluable subjects (i.e., those meeting all eligibility criteria, complying with the procedures defined in the protocol, and fulfilling requirements for analysis defined in the RAP) for whom data concerning efficacy endpoint measures are available. Note that for the primary endpoint of the trial only those children in Cohort 1 will contribute.

***Total cohort analysis of safety***

The Total Cohort will include all subjects enrolled in the study for whom data concerning safety endpoint measures are available.

***Protocol-defined cohort for analysis of safety (ATP)***

All reactogenicity analyses will be performed for the Total Cohort.

***Total cohort analysis of immunogenicity***

The Total Cohort will include all subjects enrolled in the study for whom data concerning immunogenicity endpoint measures are available.

***Protocol-defined cohort of immunogenicity (ATP)***

The protocol-defined cohort for analysis of immunogenicity will include all evaluable subjects (i.e., those meeting all eligibility criteria, complying with the procedures defined in the protocol) for whom data concerning endpoint measures are available.

## Estimated sample size

### Cohort 1

The primary objective of this study is to assess the efficacy of the RTS,S/AS02A malaria candidate vaccine against clinical episodes of malaria fitting the primary case definition. 704 evaluable subjects per group are needed in order to have 80% power to detect a lower 95% confidence limit of vaccine efficacy of approximately 15%, assuming a likely *P. falciparum* attack rate during the surveillance period of 11% in the control group and vaccine efficacy of 50% (Table 5). Sample size calculation is done using a method proposed by BlackWelder[[34]](#endnote-35). Taking into account a level of 10% of non-evaluable subjects (e.g. protocol non-compliance, dropout during vaccination schedule), at least 782 subjects should be recruited in each group.

The attack rate estimate of 11% for the control group is derived from a demographic surveillance system in the CISM surveillance area and the morbidity surveillance system at Manhiça Hospital, which has been in operation since mid 1996. The estimate is the average of the attack rates over the last four years (yearly periods of 1998 to 2001). A sample size of 704 per group will provide strong statistical evidence of a treatment benefit (if it exists given the attack rate and vaccine efficacy estimates) at a p value level of 0.002. These sample size estimates were also reproduced using a simulation program that simulates the incidence of clinical malaria episodes based on the maximum likelihood estimate of the hazard assuming a Gompertz distribution of the survival time.

*Algorithm for Sample size program*

- Survival times assuming Gompertz distribution was found to provide the best fit to previously observed data (clinical malaria by passive case detection in children 1 to 4 years of age from 1998-2001). Thus survival in the control group is estimated as: h(t)=exp(λ)*exp(γt),
  where ***h(t) is the hazard function and*** λ and γ are the parameters of the distribution. These parameters are maximum likelihood estimators of the Gompertz fitted model.
  **(Amended January 17, 2003)**
- Based on the survival function:
  ~~S(t) = exp(-exp(λ)/γ*(exp(log(1-log(s)*g/exp(l))/g*t)-1)),~~
  ***S(t)=exp{-exp(λ)*[exp(γ*t)-1]/ γ }***
  random samples from the survival time are drawn taking random samples from the cumulative probability distribution F(t) = 1-S(t). Values from F(t) are simulated using an random uniform distribution between 0 and 1 and converted into survival times using the equation:
  ***t =*** log(1-log(S(t))*γ/exp(λ))/γ
  **(Amended January 17, 2003)**
- The model in the vaccinated group is estimated as:
  h(t)=exp(λ+log(1-VE))*exp(γt)
  where VE is the vaccine efficacy. The procedure to simulate survival times is similar to the method described for the control group above.
- For each simulated trial, an analysis using Cox regression models is made. For this analysis, survival times are censored at 180 days. The empirical power (EP15) is calculated as the proportion of trials where the lower limit of the 95% CI estimate of the VE is greater than 15%. Every set of conditions (N) is simulated 10 000 times to obtain a precision of empirical power.

A sample size of 700 will have 81.5% power to detect a lower confidence interval of the vaccine efficacy greater than 15%, assuming an average rate of clinical malaria (defined as axillary temperature  37.5°C plus parasitaemia greater than 2500 parasites per µl).

Table 5: Sample size to establish the lower limit of the 95% CI of vaccine efficacy in Cohort 1

| Vaccine efficacy (%) | Attack rate (%) | Lower limit of 95% CI of vaccine efficacy (%) | Number of subjects per group |
| --- | --- | --- | --- |
| 50 | 11 | 30 | 1752 |
| 25 | 1207 |
| 20 | 898 |
| 15 | 704 |
| 10 | 574 |
| 5 | 481 |
| 0.5 | 419 |

There is no plan to extend enrolment in the event that the attack rate is lower than predicted over the period during which the trial will be conducted. If the rate was equal to the lowest recorded in the averaged four yearly rates i.e. 7%, the trial would still be highly powered to detect a difference between groups (power = 80% at the 5% level of significance) but the precision of estimate of effect would be less.

The trial is designed to provide precision about the estimate of effect if the true vaccine efficacy is 50%. This level of efficacy is of prime interest for guiding future development decisions. In the event that the true vaccine efficacy is less, the trial remains sufficiently powered to detect a difference but not to define this with precision. For example, if true vaccine efficacy is 45% the trial will have a power of 90% to detect a difference at the 5% level of significance and similarly if true vaccine efficacy is 40% the trial will have power of 81% at the 5% level of significance.

In addition to the primary objective, data will be analyzed to determine the time to first clinical presentation of a haematocrit below 25%. The average attack rate for anaemia (as defined as a haematocrit of less than 25%) at the Manhiça District Hospital between 1998 to 2001 was 6% over 6 months. A sample size of 704 per group will achieve 68% power to detect a difference of 0.03 between the null hypothesis that both group proportions are 0.06 and the alternative hypothesis that the proportion in the RTS,S/AS02A group is 0.03 using a two-sided log rank test with a significance level of 0.05.

(Sample size calculations were performed using NCSS trial and Pass 2000).

### Cohort 2

The overall aims for Cohort 2 of the study are two fold:

- to assess the efficacy of the RTS,S/AS02A malaria candidate vaccine in delaying time to first asexual falciparum infection.
- to compare the humoral response for anti-HBs antibodies induced by the RTS,S/AS02A malaria candidate vaccine with the humoral response to Engerix-B™ (hepatitis B vaccine).

Table 6 presents the sample sizes required to detect a vaccine efficacy of 50% in the prevention of new infections. A study with a sample size of ***166*** ~~142~~ evaluable subjects per group will have an ***86*** ~~80~~% power to detect a lower confidence interval of 20%. The age distribution of Cohort 2 will reflect that of Cohort 1.

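### The stated 68% power for time to first clinical anaemia is not the power of the test described: a two-sided 5% log-rank test of 6% against 3% with 704 per group has about 78%

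*Supplement*

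**What the plan says.** Section 10.6.1 of the protocol sizes Cohort 1 on the primary endpoint: "704 evaluable subjects per group are needed in order to have 80% power". The recruitment target is then raised: "Taking into account a level of 10% of non-evaluable subjects", at least 782 are to be recruited per group. The 704 is therefore a count of evaluable children.

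The same section then gives one power statement for clinical anaemia, a secondary endpoint in section 10.3.1. The background attack rate at the district hospital "between 1998 to 2001 was 6% over 6 months". The statement reads "A sample size of 704 per group will achieve 68% power to detect a difference of 0.03". Its null is given as "the null hypothesis that both group proportions are 0.06"; under the alternative, "the proportion in the RTS,S/AS02A group is 0.03". The comparison is to be made "using a two-sided log rank test with a significance level of 0.05". Allocation is equal (section 3). The anaemia statement mentions no further loss, no other significance level and no continuity correction.

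**The concern.** The sentence contains everything needed to compute the power, and the result does not match. The printed 68% implies a type II error of 32%; the test as described has about 22%.

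This is the only power given for the clinical anaemia endpoint. A reader who trusts 68% would treat a null anaemia result as what one expects from an underpowered comparison. At about 78% the same result is moderately informative. The figure also sits beside three other powers at the 5% level in section 10.6.1 (80%, 90% and 81%) that can be reproduced, so it is the odd one out.

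**Working it through.** **Inputs, all from the protocol.** n = 704 per group, 1:1; six-month risks of 0.06 and 0.03; log-rank test, two-sided, alpha = 0.05 (z = 1.960).

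**Events and effect size.**
- Expected events: 704 × (0.06 + 0.03) = 63.4.
- Hazard ratio: ln(0.97) / ln(0.94) = 0.492.

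**Power of the log-rank test as described.**
- Freedman: √63.4 × (1 − 0.492)/(1 + 0.492) = 2.71; 2.71 − 1.96 = 0.75; power 77.3%.
- Schoenfeld: |ln 0.492| × √(63.4/4) = 0.709 × 3.98 = 2.82; 2.82 − 1.96 = 0.86; power 80.5%.
- Simulated log-rank test (exponential times, censored at six months, 20,000 trials): 78.0%. A separate run of 10,000 trials gave 78.3%.
- Taking the hazard ratio as exactly 0.50: Freedman 75.6%, Schoenfeld 78.8%.

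For 68% log-rank power, about 522 (Schoenfeld) to 566 (Freedman) children per group would be enough.

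**Attempts to reproduce 68% on the stated inputs.**

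| Variant (704 per group, two-sided 0.05 unless noted) | Power |
|---|---|
| Two proportions, pooled variance | 77.6% |
| Two proportions, unpooled variance | 77.7% |
| Arcsine | 78.6% |
| Two proportions, continuity-corrected | 73.5% |
| Fisher's exact test | 74.4% |
| Log-rank, one-sided 0.05 | 84–88% |
| Log-rank, 704 read as the total | 47–51% |
| Log-rank, 782 per group | 80–84% |

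None is within 2 points of 68%.

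**What does give about 68%.**

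| Changed condition | Power |
|---|---|
| Log-rank (Freedman), two-sided 0.025 | 68.0% |
| Pooled proportions, two-sided 0.025 | 68.3% |
| Log-rank (Freedman), a further 20% lost from the 704 | 67.8% |
| Continuity-corrected proportions, a further 10% lost | 68.5% |
| Proportions, null variance fixed at 0.06 in both groups | 68.1% |

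The first four need a level, or a loss beyond the 704 evaluable children, that the anaemia statement does not give. The 10% allowance has already been spent (704/0.9 ≈ 782), and section 1.2.2.5 applies the 20% rate to Cohort 2 only. The fifth is not a log-rank test.

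**Neighbouring powers in section 10.6.1.** A continuity-corrected comparison of two proportions at 704 per group reproduces all three; the fixed-null-variance method does not.

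| Scenario | Printed | Continuity-corrected | Null variance fixed at control rate |
|---|---|---|---|
| Attack rate 7%, efficacy 50% | 80% | 80.7% | 75.9% |
| Attack rate 11%, efficacy 45% | 90% | 89.9% | 87.2% |
| Attack rate 11%, efficacy 40% | 81% | 80.6% | 77.4% |
| Anaemia, 6% against 3% | 68% | 73.5% | 68.1% |

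**The case against.** The strongest reply starts from the text's own null hypothesis, that both proportions are 0.06. Taken literally in a test of proportions, the null standard error is √(2 × 0.06 × 0.94/704) = 0.01266 and the alternative standard error is √((0.06 × 0.94 + 0.03 × 0.97)/704) = 0.01102. The power is Φ((0.03 − 1.96 × 0.01266)/0.01102) = 68.1%, with no change to n, alpha or loss. On this reading the number may be a conservative proportions calculation that was labelled log-rank, and the label rather than the figure would need correcting. This stands as a candidate source. It does not rescue the sentence, because a proportions formula with an assumed null variance is not the log-rank test named, and the same formula misses the three neighbouring figures.

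Two further points have some force. First, the 10% allowance is illustrated by non-compliance and dropout during vaccination, and section 10.7.2.1 censors withdrawals and deducts absences and post-treatment periods from time at risk. The 78% assumes complete follow-up of all 704 and is therefore an upper figure on the stated rates; the documents give no surveillance-period loss rate with which to size the shortfall. Second, against the method that appears to lie behind the neighbouring powers, the gap is about 5.5 points (73.5% against 68%) rather than 10.

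It is also fair to say that the consequence is limited. The error is conservative, no decision rule uses the figure, and a null result would be judged mainly from the confidence interval.

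**Conclusion.** The concern holds. For the test as written, power is about 78% (76% to 81% across the log-rank methods), so the printed 68% is about 10 points too low. Even the least favourable standard variant on the stated inputs, a continuity-corrected comparison of proportions, gives 73.5%. The result assumes the protocol's rates, 1:1 allocation, proportional hazards with the ratio implied by the two risks, and follow-up of all 704 evaluable children over six months. That the figure is inconsistent with the described test is firm; where 68% came from cannot be settled from the documents. Power is understated, and the Cohort 1 sample size is unaffected.

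**What to change.** In section 10.6.1, replace the 68% with about 78% for 704 per group, 6% against 3%, two-sided log-rank test at 0.05. If 68% was intended, keep it and state what produces it: the significance level, the additional loss with the matching number per group, or the proportions method and its variance assumption in place of the log-rank label. This changes one sentence of the protocol. Enrolment and analysis stay as they are.
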